## Abstract

**Background:**

Effective yet practical strategies are needed to increase engagement in HIV treatment and prevention services, particularly in high-HIV-prevalence hotspots. We designed a community-based intervention called “Health Scouts” to promote uptake and adherence to HIV services in a highly HIV-prevalent fishing community in Rakai, Uganda. Using a situated Information, Motivation, and Behavioral skills theory framework, the intervention consists of community health workers, called Health Scouts, who use motivational interviewing strategies and mobile health tools to promote engagement in HIV treatment and prevention services.

**Methods/design:**

The Health Scout intervention is being evaluated through a pragmatic, parallel, cluster-randomized controlled trial with an allocation ratio of 1:1. The study setting is a single high-HIV-prevalence fishing community in Rakai, Uganda divided into 40 contiguous neighborhood clusters each containing about 65 households. Twenty clusters received the Health Scout Intervention; 20 clusters received standard of care. The Health Scout intervention is delivered within the community at the household level, targeting all residents aged 15 years or older. The primary programmatic outcomes are self-reported HIV care, antiretroviral therapy, and male circumcision coverage; the primary biologic outcome is population-level HIV viremia prevalence. Follow-up is planned for about 3 years.

**Discussion:**

HIV treatment and prevention service engagement remains suboptimal in HIV hotspots. New, community-based implementation approaches are needed. If found to be effective in this trial, the Health Scout intervention may be an important component of a comprehensive HIV response.

**Trial registration:**

ClinicalTrials.gov, ID: NCT02556957. Registered on 20 September 2015.

**Electronic supplementary material:**

The online version of this article (doi:10.1186/s13063-017-2243-6) contains supplementary material, which is available to authorized users.

## Background

Combination HIV prevention (CHP) is the application of multiple HIV-prevention interventions, such as antiretroviral therapy (ART), and male circumcision (MC), to maximize population-level impact on HIV incidence [1, 2]. Treatment and prevention service cascades—which depict engagement and loss of service users and people living with HIV along the continuum of service delivery—have fostered skepticism about whether high CHP coverage goals are realistic [3–5], and highlight the need for effective and sustainable implementation strategies that are not primarily facility-based [6]. Current studies to evaluate CHP mostly involve well-resourced approaches, limiting reproducibility and sustainability [7]. Empirical testing of CHP implementation approaches that are practical and community-based are, therefore, needed.

HIV hotspots are geographically defined areas of extremely high HIV transmission and prevalence. Hotspots are found throughout sub-Saharan Africa (e.g., certain mining and fishing communities), and may compromise national and regional HIV prevention efforts [8–17]. The President’s Emergency Plan for AIDS Relief (PEPFAR), the Joint United National Program on HIV/AIDS (UNAIDS), and the World Health Organization (WHO) have made HIV hotspots a central focus of their HIV response [18–20]. However, rigorous evidence on comprehensive and effective CHP strategies for hotspots is limited and, therefore, a priority research need [7]. Many Lake Victoria fishing communities, the setting for this trial, are hotspots due to a number of factors increasing HIV risk, including high rates of condomless sex, multiple sex partners, prominent sex work, and prevalent alcohol misuse [10, 21].

Fishing communities represent a critical challenge to HIV prevention in Uganda and the wider region. The fishing community hosting this research has the highest HIV prevalence, approximately 40%, ever reported from the Lake Victoria region [21]. It is a place where HIV prevention and service needs are great, yet resources and health system infrastructure are modest. A community-based approach offers an opportunity to work with the community to devise potential solutions to HIV-related challenges. Successful HIV efforts in this setting may provide a model for similar settings.

Community health workers (CHWs), using mobile health technologies (mHealth) and motivational interviewing (MI) strategies to tailor intervention messaging, may represent a high-impact and sustainable CHP implementation strategy, particularly in HIV hotspots [22–26]. CHW impact could be optimized by mHealth tools as sub-Saharan Africa has some of the fastest mobile phone growth rates in the world [27, 28]. CHW effectiveness could be further enhanced using evidence-based, MI counseling techniques that emphasize a client-centered approach. We therefore designed the “Health Scouts” mLAKE trial (mHealth Lakefolk Actively Keeping Engaged) which is a CHW-based, mHealth-supported, MI-informed, theory-based CHP implementation intervention being evaluated in an HIV hotspot fishing community in Rakai, Uganda. MI was chosen as the foundation of the CHW counseling strategy because of its cross-cultural robustness, and effectiveness with heterogeneous populations [29, 30]. HIV hotspots may particularly benefit from the MI techniques which emphasize taking into consideration complex contextual factors influencing client behaviors. mHealth could be of particular benefit in this setting in assisting CHWs through complicated counseling algorithms for individuals with multiple areas of HIV risk.

Here, we present the study protocol for the mLAKE trial which began recruitment in September 2015 with follow-up planned until at least 2018. The objective of the study is to determine the impact of the CHW intervention on important HIV-related treatment and prevention outcomes, i.e,. HIV service uptake and population prevalence of viremia. This study is being conducted in a hotspot fishing community because of the need for more effective interventions to improve treatment and prevention in high-HIV-burden, high-HIV-risk settings. The protocol format is guided by the Standard Protocol Items: Recommendations for Interventional Trials (SPIRIT) Checklist (Additional file 1) and the Consolidated Standards of Reporting Trials (CONSORT) extension to cluster-randomized trials [31, 32].

## Methods/design

### Study setting

The intervention setting is a fishing community (area approximately 2 km^2^, adolescent/adult population approximately 4400) on Lake Victoria in Rakai District in south-central Uganda. Rakai District is bordered to the south by Tanzania and to the east by Lake Victoria. The fishing community is approximately 235 km from Kampala, the capital of Uganda. Since 2011, the Rakai Health Sciences Program (RHSP) has been the primary provider of CHP services in this fishing community. These services include community-based demand generation (e.g., mass media such as radio-talk shows, community meetings, and drama shows), an HIV clinic which provides free pre-ART and ART care, community-based HIV testing, and mobile MC camps. In this community, ART is initiated at time of diagnosis, irrespective of CD4 count (i.e., test and start strategy) as fisherfolk have been designated a key population by the Ugandan Ministry of Health. The HIV prevalence in this community is approximately 40%.

### Trial design overview

The impact of the Health Scout intervention will be assessed through a pragmatic, parallel, cluster-randomized controlled trial with an allocation ratio of 1:1 and superiority framework (Fig. 1). The cluster-randomized design was chosen over other study designs as individual and household randomized designs were logistically difficult to implement and increased contamination risks; quasi-experimental designs were deemed less rigorous.

**Fig. 1 Fig1:**
[figure not shown]
The mHealth Lakefolk Actively Keeping Engaged (mLAKE) study flow diagram

#### Cluster design

The largest of the fishing communities in the region was selected for the mLAKE trial and 40 was chosen as the number of randomization units. There were several reasons for choosing 40 units or clusters. First, we anticipated 10 Health Scouts being deployed, each of whom would initially be allocated the same number of clusters. Some variation in the type of clusters Health Scouts were assigned was desirable to enable more robust analytic inferences on Health Scout effects. Thus, each Health Scout needed to have at least two assigned clusters. As progressively larger number of clusters increased implementation complexity and risk of contamination, we selected 40 clusters, the minimum number needed to assign each Health Scout two clusters.

The 40 clusters were then defined with consideration of implementation logistics, minimizing contamination, and geographic features such as roads, buildings, and the lake shoreline. Specifically, high-resolution satellite images of the community were digitized in ArcGIS 10.3 (ESRI, Redlands, CA, USA). Household GPS locations from a baseline community census conducted in mid-2015 were overlaid on the digitized map and the community was divided into 40 contiguous clusters (Fig. 2) each containing roughly the same number of eligible households and participants. Each cluster was estimated, using census data, to contain approximately 65 households with approximately 1.65 persons aged over 15 years (target population) in each household or approximately 107 potential eligible clients per cluster. Community-based participatory walks with the Health Scouts were conducted to confirm and refine cluster boundaries prior to participant enrollment [33].

**Fig. 2 Fig2:**
[figure not shown]
mHealth Lakefolk Actively Keeping Engaged (mLAKE) trial cluster map (intervention: clear, control; grayed)

### Pragmatic design considerations

The study design is pragmatically oriented as our primary goal is to understand if the Health Scout intervention works under usual-care conditions. To explicitly describe the pragmatic characteristics of the trial, we used the PRECIS-2 tool (Table 1). This tool is a method for scoring trials on an explanatory to pragmatic continuum across nine domains. Figure 3 shows a visualization of these scores via the PRECIS-2 wheel [34].

**Table 1 Tab1:** PRECIS-2 scores for the mHealth Lakefolk Actively Keeping Engaged (mLAKE) trial

Domains	Score^a^	Rationale
Eligibility	5	All residents ≥ 15 years of age are eligible for study participation, identical to usual care
Recruitment	4	Recruitment effort (community sensitization, drama shows, and Health Scouts approaching residents) is likely modestly above what would be expected in usual care
Setting	4	The setting is mostly similar in key characteristics (e.g., high-risk population) to other usual-care settings
Organization	3	The care delivery organization is likely much higher resourced than most usual-care organizations but efforts were made to replicate more usual-care resource capacity
Flexibility (delivery)	5	Flexibility is anticipated to be the same in how the intervention is delivered in the trial and flexibility anticipated in usual care
Flexibility (adherence)	5	No special trial measures to promote participant participation with Health Scout intervention
Follow-up	3	Participants being surveyed every at regular intervals in this trial which may be different from other settings
Primary outcome	5	Outcome is very directly relevant to participants
Primary analyses	5	All data will be included in the analysis of the primary outcomes

^a^PRECIS 5-point Likert Scale, 1 = very explanatory, 2 = rather explanatory, 3 = equally pragmatic/explanatory, 4 = rather pragmatic, 5 = very pragmatic

**Fig. 3 Fig3:**
[figure not shown]
PRECIS-2 wheel for the mHealth Lakefolk Actively Keeping Engaged (mLAKE) trial

### Study hypotheses

The study hypotheses are that residents in clusters receiving the Health Scout intervention will have improved HIV service uptake (HIV care, ART, and MC) and decreased HIV population viremia prevalence (PVP) compared to residents in control clusters who do not receive the intervention.

### Health Scout intervention

#### Conceptualization

The general approach to the design and implementation of the Health Scout intervention is *pragmatically* oriented [34]. That is, a framework for Health Scout recruitment, training, tasks, quality assurance, and monitoring was developed, but the intervention is designed with flexibility to adapt to the needs, constraints, and secular changes during implementation. The framework included the following core components: (1) CHW (Health Scout)-based delivery; (2) counseling using MI strategies; (3) household-based delivery; and (4) mHealth-support. A situated Information, Motivation, and Behavioral Skills (sIMB) theory-based conceptual framework was developed wherein Health Scouts would promote relevant tailored information, motivation, and behavioral skills to improve clients’ engagement in HIV treatment and prevention services, ultimately leading to improved HIV-related outcomes, including decreased HIV incidence (Fig. 4) [35, 36].

**Fig. 4 Fig4:**
[figure not shown]
Health Scout intervention conceptual framework

#### Implementation

Ten Health Scouts were recruited from the community and underwent residential- and field-based training. Residential training focused on mHealth application/smartphone use, confidentiality, disclosure, and CHP- and HIV-related knowledge. Field-based training focused on mock counseling role play, cluster boundary walk-throughs, and filling out Home Visit Forms. MI skills, a communication strategy that emphasizes a non-judgmental and non-confrontational approach to behavior change, were integrated into Health Scout training. After demonstrating basic competency with their assigned tasks, Health Scouts attempted to visit all “clients” (i.e., residents aged 15 years and older, any gender) within their clusters within 3 months of study initiation and follow-up each eligible client within their cluster every 3 months for approximately 3 years. During each visit, Health Scouts counsel clients with assistance from a smartphone application. Visits are anticipated to take approximately 30–45 min. Each Health Scout was assigned two clusters containing approximately 215 total eligible clients. Health Scouts were provided compensation for their activities.

#### Health Scout smartphone application

The Health Scout smartphone application (Fig. 5) functions as a decision and counseling support tool to guide Health Scouts through the sIMB- informed counseling session (emocha Mobile Health Inc., Baltimore, MD, USA). Using simple forms, the application takes the Health Scout through three steps: (1) household screening-household members are screened for age eligibility; (2) individualized counseling triage – residents who are age-eligible are then individually asked a series of triage screening questions, e.g., age, gender, HIV status, to determine which counseling modules should be activated; and, (3) MI counseling-tailored counseling modules with MI-informed prompts and messages are provided for the Health Scout to review with the client. The application contains nine counseling modules as shown in Table 2 (Additional file 2). Figure 6 provides a sample schematic of the counseling module content for a client who knows that they are HIV-positive, but is not yet in care.

**Fig. 5 Fig5:**
[figure not shown]
Example screenshots from Health Scout smartphone application

**Table 2 Tab2:** Health Scout mHealth application counseling modules

#	Module description
1	HIV serostatus unknown or no recent HIV test, male or not pregnant female
2	HIV serostatus unknown or no recent HIV test, pregnant female
3	Male, not circumcised
4	HIV+, not in care
5	HIV+, in care, not on antiretroviral therapy (ART)
6	HIV+, on ART
7	HIV+, pregnant
8	Male having condomless sex
9	Female having condomless sex

**Fig. 6 Fig6:**
[figure not shown]
Example of counseling module flow and content: HIV-positive, not yet in care

### Control arm description

Household residents in both study arms will have access to standard of care RHSP HIV prevention and treatment services as described in the “Study setting” section above. Health Scouts are not prohibited from interacting with control arm residents but cannot conduct mHealth-supported counseling home visits with residents outside of the intervention clusters.

### Outcomes

The mLAKE trial has three primary programmatic outcomes (HIV care, ART, and MC coverage), one primary biologic outcome (HIV population viremia prevalence (PVP)), and several secondary outcomes (Table 3). PVP, variously termed community viral load, population viral load, or population prevalence of detectable viremia, was chosen as the primary biologic outcome because it is strongly correlated with HIV incidence [37]. The programmatic outcomes are all key indicators for major HIV service programs and funders.

**Table 3 Tab3:** Descriptions of mHealth Lakefolk Actively Keeping Engaged (mLAKE) trial primary (1°) and secondary (2°) study outcomes^a^

	Outcome	Description	Numerator/event	Denominator
1°	HIV care coverage^b^	Proportion	# linked to HIV care	# HIV-positive
1°	ART coverage^b^	Proportion	# on antiretroviral therapy (ART)	# HIV-positive
1°	MC coverage^b^	Proportion	# non-Muslim men circumcised	All non-Muslim men aged 15–49 years
1°	HIV population viremia prevalence (PVP)	Proportion	HIV+ c VL > 400	All study participants
2°	HIV incidence	Rate	# new HIV infections	HIV-negative person-years
2°	HTS coverage	Proportion	# ever tested and received HIV results	All study participants
2°	ART treatment failure^c^	Proportion	Composite: virologic failure *or* Mortality *or* lost to follow-up *or* stopped ART	# initiated on ART
2°	Consistent condom use^b^	Proportion	# using condoms consistently past 12 months	# sexually active

^a^Outcomes described at the cluster level; outcomes may also be analyzed at the individual level

^b^Self-reported

^c^Outcomes will also be individually analyzed. Virologic failure = any viral load (VL) > 1000 copies/mL. Lost to follow-up = no clinic visit > 180 days

*ART* antiretroviral therapy, *HTS* HIV Testing Services, *MC* male circumcision

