#### Sequence generation, allocation concealment mechanism, and implementation

Given the fixed sample size and desire for baseline comparability of important characteristics, we used restricted randomization to allocate intervention arms [39]. First, we defined a priori that we would accept up to 7.5% difference in baseline cluster level characteristics (including percentage of residents aged 20–29 years in the cluster, percentage of women) and in primary study outcomes (including cluster level percentage of men circumcised, percentage of HIV-positive persons in care, percentage of HIV-positive persons taking ART, percentage HIV PVP). The 7.5% threshold was chosen for simplicity, consistency, and face validity. Second, we conducted 2500 independent, simple, computer-generated randomizations, assigning 20 clusters to one arm (coded as 0) and 20 clusters to a second arm (coded as 1). Third, among the 2500 randomizations, those who did not satisfy the above comparability criteria were removed, resulting in 455 eligible randomizations. Fourth, from the 455 randomizations, one randomization sequence was randomly drawn for allocation of intervention. Final assignment of arms (0 and 1) to intervention and control was done in a public coin-flip ceremony witnessed by study staff and the Health Scouts.

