### Sample size/power

The sample size for this trial is fixed. Therefore, the relevant study power-related question was to estimate whether the trial had reasonable chance to detect public health-relevant differences in primary study outcomes, i.e., minimum detectable differences (MDD). Baseline data from a mid-2015 RCCS survey of the fishing community were used to first estimate the coefficients of variation (CV) or intracluster correlation coefficients (ICC) (Table 4). We then used prior data from 9–10/2013 (approximately 18 months prior to the mid-2015 data) to project the expected prevalence of the primary outcomes expected for the control arm at the end of the trial (Table 4). The mLAKE trial is planned for approximately 36 months of follow-up, i.e., two RCCS rounds after the baseline 2015 round. The assumption is that 2013 through 2015 were times of rapid scale-up of CHP service access and that this momentum will slow (roughly by 50% for MC, HIV care and by 75% for PVP, ART, and HIV incidence) over the next 36 months.

**Table 4 Tab4:** Power calculation parameters and derivation of control arm outcome estimates at the end of the trial

Characteristics	CV	ICC	2013	2015	2013 to 2015 ∆	Proposed control arm outcome
Population viremia prevalence (PVP)	0.33	0.02	25%	16%	9%	11.2%
HIV care coverage	0.141	0.061	70%	75%	4.8%	80.1%
ART coverage	0.187	0.072	43%	67%	24.6%	79.7%
MC coverage	0.209	0.062	52%	59%	8.1%	66.9%
HIV incidence	0.929	NA	3.34	2.9	0.44	2.7

*ART* antiretroviral therapy, *MC* male circumcision, *NA* not applicable

MDDs were subsequently calculated with 80% power as described by Hayes and Moulton (Table 5) [39]. Potential impact of contamination was also assessed by assuming 10–50% of control arm residents would be influenced by the intervention. Based upon these calculations, the study should have MDD ratios with 80% power to be able to detect a 41% or greater decrease in PVP, 15% or greater increase in HIV care coverage, 20% or greater increase in ART coverage, and 23% or greater increase in MC coverage. Study power was considered reasonable by the study team for all primary outcomes.

**Table 5 Tab5:** Calculation of minimum detectable difference (MDD) for the mHealth Lakefolk Actively Keeping Engaged (mLAKE) trial

Outcome	Control proportion	% Contamination	Control proportion + contamination	Intervention proportion	MDD ratio	MDD difference
PVP	0.112	0	0.112	0.066	0.593	−0.046
PVP	0.112	0.1	0.107	0.063	0.559	−0.049

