### Statistical methods

The comparability of intervention and control arms will be assessed at baseline. Two-sample *t* tests will be used to compare the baseline cluster-level outcomes (individual-level data at baseline are not available for participants absent from the baseline survey). Additionally, participant demographics (age, sex) are known risk factors for the study outcomes, and will be assessed for comparability. If a baseline outcome or demographic variable are significantly different between arms with *p* value ≤ 0.1, adjusted regression analysis on the outcome variables will be conducted adjusting for baseline covariates.

The cluster-level data for study outcomes will be presented by survey and by arm. The primary analysis will be by intent-to-treat and use generalized linear models (GLM) with generalized estimating equation (GEE) to account for within-cluster correlations. Specifically, the logistic model with GEE will be used for binary outcomes (e.g., PVP, MC, ART), and Poisson log-linear model with GEE will be used for the HIV-incidence outcome. Exchangeable correlation structure will be used in the GEE models. Separate analysis will be conducted for each RCCS follow-up survey to assess the shorter- and longer-term effect of the intervention.

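### The PVP model fixes no baseline covariate, so chance variation in cluster HIV prevalence that the plan could remove stays in the estimate and costs precision

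*Protocol article*

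**What the plan says.** - **Outcome.** In Table 3, PVP counts HIV-positive people with a viral load above 400 and divides by "All study participants". HIV care and ART coverage divide by HIV-positive people only. The Outcomes text says that "PVP, variously termed community viral load, population viral load, or population prevalence of detectable viremia, was chosen as the primary biologic outcome"; the reason it gives is the correlation of PVP with incidence.
- **Randomization.** Allocations were kept only if the arms agreed within 7.5% on age 20–29, sex, men circumcised and "percentage of HIV-positive persons in care, percentage of HIV-positive persons taking ART, percentage HIV PVP". HIV prevalence is not listed.
- **Analysis.** Statistical methods specifies a logistic GEE by intention to treat. Baseline outcomes are compared between arms. The text adds that "participant demographics (age, sex) are known risk factors for the study outcomes" and will also be checked. Adjustment follows only where one of these differs at p ≤ 0.1. HIV prevalence is again not listed, and no covariate is fixed in advance.
- **Planning values.** Table 4 gives PVP a CV of 0.33, a 2015 value of 16% and a projected control value of 11.2%. The CVs come from the mid-2015 survey of this community. Study setting puts HIV prevalence at about 40%.

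**The concern.** An arm that by chance holds more HIV-positive residents has higher PVP even when suppression is identical. Baseline HIV prevalence predicts this and the RCCS already measures it, yet the plan never uses it by name. Adjustment for anything else waits on a significance test of baseline balance. Such a test does not ask whether a covariate predicts the outcome, which is what determines the gain in precision. At stake is the width of the interval for the only biologic primary outcome, which has 80% power only for a reduction of about 41%.

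**Working it through.** **1. The plan's own figure.** Inputs: 20 clusters per arm, control PVP p0 = 0.112, k = 0.33, power 80%, two-sided α = 0.05 (assumed; not stated). Solve for p1 in

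20 = 1 + (1.96 + 0.84)² × [p0(1−p0)/m + p1(1−p1)/m + k²(p0² + p1²)] / (p0 − p1)².

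The cluster size m used in Table 5 is not stated. With m = 50, p1 = 0.0662 (ratio 0.591); with m = 51 the ratio is 0.594. The article gives 0.066 and 0.593, so the figure is reproduced. The same m also returns the stated values for care (0.920), ART (0.952) and circumcision (0.822). With all 107 eligible people per cluster the ratio would be 0.659. The CV and ICC also agree: 0.33² × 0.16/0.84 = 0.021, against 0.02 in Table 4.

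**2. Decomposition.** The control viremic fraction is 0.112/0.40 = 0.28. The per-person sampling variance of log PVP is (1−0.40)/0.40 + (1−0.28)/(0.28 × 0.40) = 1.50 + 6.43 = 7.93. Prevalence contributes 1.50/7.93 = 19% before any between-cluster variation.

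**3. Size of chance imbalance.** SE of the arm difference in prevalence = √[2 × (0.24/(20m) + SD²/20)], where SD is the between-cluster SD of prevalence (not given; assumed). At m = 50:
- SD 0: √[2 × 0.00024] = 2.2 points
- SD 5 points: √[2 × (0.00024 + 0.000125)] = 2.7 points
- SD 8 points: √[2 × (0.00024 + 0.00032)] = 3.3 points

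A difference of 1.96 SE moves PVP by 1.96 × 2.2 × 0.28 = 1.2 points at SD 0 and by 1.96 × 3.3 × 0.28 = 1.8 points at SD 8, or 11% and 16% of 11.2%. Over m = 50–107 and a prevalence ICC of 0–0.05 the range is 7–20%. The detectable difference is 4.6 points.

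**4. What the existing safeguards do.** The SE of the baseline PVP difference is √[2 × (0.16 × 0.84/m + (0.33 × 0.16)²)/20] = 2.3 points (m = 50) or 2.0 points (m = 107).
- If the 7.5% limit is in absolute points, it is met more than 99.8% of the time and does almost nothing for PVP.
- If it is relative (0.075 × 16% = 1.2 points), it is met 39–45% of the time. In simulation it lowers the SE of the prevalence difference by only 4–16%, for example from 3.3 to 2.8 points at m = 50 and SD 8.
- The p ≤ 0.1 trigger needs a difference of about 1.645 × 2.3 = 3.8 points. On the relative reading the restriction has already excluded that, and in simulation the trigger never fired for PVP (smallest p about 0.35).

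The observed acceptance of 455/2,500 = 18.2% fits the relative reading better: treating the four outcome criteria as independent gives 13–19% on that reading and 67–77% on the absolute one.

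**5. Gain from a fixed covariate.** Simulation of 20 v 20 clusters, m = 50 or 107, total PVP CV held at 0.33, 70% of residents common to both surveys (assumed), cluster-level regression:

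| Cluster prevalence SD | Variance cut from adjusting for baseline prevalence |
|---|---|
| 0 points | about 1–2% |
| 5 points | about 7–10% |
| 8 points | about 15–20% |

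A second set-up with the same CV at m = 50 gave 5–8% at SD 5 and 14–16% at SD 8, so these figures are good to a few points.

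Power at a true ratio of 0.7, m = 50: the variance is [0.112 × 0.888/50 + 0.0784 × 0.9216/50 + 0.1089 × (0.01254 + 0.00615)]/19 = 0.000288, SE 0.0170. Then 0.0336/0.0170 − 1.96 ≈ 0.02, which is 51% power. At SD 8, adjustment for prevalence raises it to about 58%.

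**6. Adding baseline PVP.** If cluster viremia persists between surveys, the two covariates together cut the variance by up to about 23% at m = 50 and 38% at m = 107. If it does not persist, the second covariate costs about 2 points: a useless covariate inflates the variance by roughly 36/35, just under 3%. Persistence is not given in the document.

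**The case against.** **The denominator is a reasoned choice.** PVP measures viremic people in the population and was chosen for its link with incidence. Viremia among HIV-positive people answers a different question. This stands, and PVP should remain primary.

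**Prevalence is not uncontrolled.** A reader might infer that prevalence differences pass unchecked into the effect. That is too strong: baseline PVP contains prevalence, was a restriction variable, and is a candidate for adjustment. Step 4 shows only that this control is weak and indirect.

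**The noise is already counted.** The CV was estimated from this community, so it includes prevalence variation. Chance imbalance is random error that the interval covers. It would be wrong to infer bias or an understated detectable difference. Nor is 41% a floor on detection: power for a 30% reduction is about 51%.

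**Prevalence is not pure nuisance.** The counselling modules also cover testing, circumcision and condomless sex. At 2.7 per 100 person-years, three years add 0.60 × (1 − e^(−0.081)) = 4.7 points, so a 20–40% cut in incidence changes prevalence by 0.9–1.8 points. Averted infections might be viremic more often than average, so the effect on PVP need not be trivial. This stands against calling follow-up prevalence a nuisance. It does not count against the mid-2015 value, which precedes the intervention and so cannot absorb its effect.

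**Baseline PVP may be the better covariate.** True where cluster viremia persists: at a correlation of 0.7 it does about as well as prevalence or better, and at 1 clearly better. Prevalence wins at low persistence. This is the reason to prefer both.

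**Covariates may be left to an analysis plan.** The article does not leave the rule open. It states one, based on baseline p values, and that stated rule is what is criticized.

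**Conclusion.** The point holds as a modest, avoidable loss of precision in the PVP analysis. It is not an error in the outcome definition, a source of bias or a fault in the power calculation. The gain is negligible if HIV prevalence barely varies between clusters and worthwhile at a between-cluster SD of 5 to 8 points. The sponsor can settle which applies, since the mid-2015 data hold that SD. The figures rest on assumed cluster SDs, an inferred m, 70% overlap and a viremic fraction that varies independently of prevalence. In the simulations adjusting for baseline prevalence never lost precision, so the recommendation does not depend on which SD is right.

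**What to change.** Keep PVP over all participants as the primary biologic outcome. In its model, always include mid-2015 cluster HIV prevalence, preferably together with mid-2015 cluster PVP, whatever the baseline p values. Report the viremic fraction among HIV-positive participants beside it as a supporting analysis, to show whether a PVP difference reflects suppression or who is HIV-positive. Fix this before data by arm are released.

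The cost is one or two degrees of freedom from 40 clusters, one extra tabulated proportion, and a sentence saying that the odds ratio is adjusted for baseline cluster values. The RCCS already collects all the data needed.
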